#### Sample Size Considerations:

Effect size: Given that the design is a within subject repeat measures analysis of variance, the overall variance should be about half of that we had originally anticipated. In fact, two recent studies were able to show significant restoration of grey matter in n=10 patients with such a design. However, in those two studies the pain relief was complete for many months. Here we expect a smaller decrease in pain (between 10-20mm on VAS scale from baseline) and, as a result, we have increased the sample size of the population treated with drug three times. Moreover, assuming that pain relief will be less in the placebo group, inclusion of this arm into the study should strengthen the power of the study. The healthy normal subjects tested at two equivalent time points is necessary to rule out that the observed results are scanner artifacts. In the normal subjects we specifically test that in the same time period and using the same scanner we observe no significant, or minimal increased atrophy (0.75 cc increase in atrophy, in the direction opposite of what we expect to see with drug treatment). Moreover, since we already have results regarding brain regions where atrophy is observed in OA, we can perform brain region-specific directed contrasts between the groups, if necessary. Overall, this design should give us enough power to test the primary and secondary hypotheses. It should be noted, however, that this is an exploratory study, and there is no statistical justification to our proposed sample size.

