The issue of atrophy due to pain in relation to changes due to aging warrants further clarification. In the 4 months of treatment all subjects should have atrophy due to aging, about  $2.5 \text{ cc} \times 0.3 = 0.75 \text{ cc}$ . On the other hand the OA cumulative atrophy over the years seems to be proportional to the number of years a given subject has had the condition. If we assume on average that the mean OA duration is 5 years, then the atrophy due to chronic pain should be about  $1.5 \text{ cc} \times 5 = 6.0 \text{ cc}$ . Therefore, in a subject where the OA pain completely disappears with treatment, that subject has the potential of exhibiting a reduction in atrophy of 6.0 cc minus the increased atrophy due to aging of 0.75 cc. Moreover, we assume that placebo responses will not induce reversal of atrophy because placebo mainly reflects attentional and motivational states of the person. There is likelihood that this assumption may not be true. Even in the latter case as we expect placebo to decrease pain less than the real drug treatment, we should still observe smaller changes in atrophy by placebo.

We consider the brain atrophy in chronic pain as an overall marker of the extent of peripheral, spinal cord, and brain reorganization a subject has developed with living and suffering with the condition. Animal models of chronic neuropathic and inflammatory pain repeatedly show that peripheral and spinal cord nociceptive transmission is dramatically changed, leading to

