#### Recruitment and Enrollment Design

Participants will be recruited from an osteoarthritis patient database available through two sites. The first site is the Rehabilitation Institute of Chicago (RIC), which the study doctor ([name]) has access to and the second site is the Northern Ohio Neuroscience, LLC, which the study doctor ([name]) has access to. They will be contacted via telephone to see if they are interested, and if so, to see if they qualify for the screening visit. All participants will complete a screening visit with either [name] or [name] to determine if they are eligible to continue in the study. Eligibility will be based on the inclusion and exclusion criteria stated below, and these criteria will be measured through a physical exam, blood tests (to screen for abnormal chemistry panels and complete blood counts, as well as pregnancy if applicable), answers participants give in their questionnaires and MRI screening forms, as well as those regarding their medical history and current medications.

Control participants will undergo a similar screening visit, except that they do not need to complete a physical exam or blood tests. If the participant is a woman of child-bearing age, then she must give urine to be used for a urine dipstick pregnancy test).

Participants will be given a written, informed consent form during the screening visit, and if they are eligible and want to participate, they will be invited to come back for subsequent visits. Note that healthy controls will only complete two visits (screening/baseline scan and the final visit involving an MRI scanning session).

Number of Subjects:

\* 80 participants with chronic osteoarthritis in their knee (20 in phase I and 60 in phase II. The 20 in phase I will all receive placebo. In phase II, 30 will receive the study drug; 30 will receive placebo)

\* 25 healthy controls

Inclusion and exclusion criteria:

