***Major inclusion criteria include:***

- \* Age: 45-80 years
- \* ACR criteria for OA including Kellgren-Lawrence radiographic OA grades II-IV
- \* VAS pain score  $\geq 5/10$  within 48 hrs of the phone screen and visit 1 (Screening)
- \* Knee OA for a minimum of 12 months
- \* Need for daily pain medication to manage symptoms of OA

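### A non-significant or 0.75 cc change in 25 healthy controls is taken to rule out scanner artefact, but it does not show absence of drift and would pass a spurious gain of about 0.75 cc

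*Protocol*

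**What the plan says.** The Recruitment and Enrollment Design section sets "25 healthy controls", scanned before and after the same four-month interval as the patients. Sample Size Considerations says that scanning them "is necessary to rule out that the observed results are scanner artifacts". The result looked for is that "we observe no significant, or minimal increased atrophy", and the accompanying parenthesis gives the amount as "0.75 cc increase in atrophy, in the direction opposite of what we expect to see with drug treatment".

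The 0.75 cc comes from Background and Rationale, where it is the expected four-month ageing loss. No tolerance around it is given, and no interval rule, SD of change, alpha or sidedness. The same section calls the study exploratory and says its sample size has no statistical justification.

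The primary hypothesis compares duloxetine with placebo, and Statistical Analysis tests it by that contrast. Controls also appear as one of three groups in a group-by-time analysis of variance. Anticipated Results adds a within-arm expectation: gray matter rises from before to after treatment on duloxetine but not on placebo.

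**The concern.** There are two problems with the criterion.

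First, failing to reject zero change is read as evidence that the scanner did not drift. The noisier the control data, the easier the check is to pass, which is the wrong way round for a safeguard.

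Second, zero is the wrong reference. If the scanner is stable, controls should lose about 0.75 cc. The criterion accepts that loss and also accepts no significant change. It therefore cannot separate a stable scanner from one that adds about 0.75 cc and masks the ageing loss. An artefact of that kind runs in the same direction as the hoped-for drug effect.

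At stake is any statement that a rise in gray matter within the duloxetine arm is real, and any comparison of patients with controls that relies on the scanner having been shown stable.

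**Working it through.** **Inputs from the protocol.** n = 25 controls. Expected ageing loss: 2.5 cc x 0.3 = 0.75 cc, which reproduces (4/12 of a year would give 0.83 cc). The number 25 has no stated derivation, so there is nothing further to reproduce.

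**Assumptions.** The SD of the four-month change is not given; I use 2, 3 and 5 cc. I take a one-sample t-test on the change, two-sided at 5%.

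**Step 1: the cancelling drift.** Net control change = drift - 0.75 cc. With drift = +0.75 cc the net change is 0. The null hypothesis of zero change is then exactly true, so the test is non-significant with probability 1 - 0.05 = 95%, whatever the SD or n. With no drift the net change is -0.75 cc, which the protocol also accepts. Both scanners pass.

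**Step 2: precision.** 95% CI half-width = t(0.975, 24) x SD/√25 = 2.064 x SD/5.

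**Step 3: power against zero.** Noncentral t with 24 df and noncentrality 5 x net change/SD.

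| Assumed SD (cc) | 95% CI half-width (cc) | Power, net 0.75 cc | Power, net 1.5 cc |
|---|---|---|---|
| 2 | 0.83 | 44% | 95% |
| 3 | 1.24 | 22% | 67% |
| 5 | 2.06 | 11% | 30% |

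These are net changes. A drift of +1.5 cc on top of a 0.75 cc loss leaves a net +0.75 cc, so the 0.75 cc column applies to it. A net +1.5 cc needs a drift of +2.25 cc. The 1.5 cc is an illustrative size; the protocol does not name it.

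**Step 4: what a pass can hide.** Suppose the observed mean control change is exactly zero, a clear pass. Estimated drift = 0 - (-0.75) = +0.75 cc, with 95% CI 0.75 ± half-width:
- SD 2: -0.08 to +1.58 cc
- SD 3: -0.49 to +1.99 cc
- SD 5: -1.31 to +2.81 cc

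**Step 5: the largest benefit in the protocol.** Background and Rationale gives 6.0 - 0.75 = 5.25 cc net gain for complete pain relief. (Its 6.0 cc is printed as 1.5 x 5, which is 7.5; that is a separate slip.) With 25 controls a net 5.25 cc change is detected with 80% power up to an SD of about 9 cc (5.25/0.584 = 8.99, where 0.584 SD is the smallest change detectable with 80% power).

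**The case against.** A reader might infer that 25 controls cannot detect drift of the size the trial looks for. The documents do not support that. It depends on an SD they do not give, and at the only benefit stated in cc, 5.25 cc, the check is well powered over a wide range of SDs. The protocol does expect less than complete relief ("Here we expect a smaller decrease in pain (between 10-20mm on VAS scale from baseline"), but it never converts that into cc. Scaling the effect in proportion to relief would be an outside assumption. What survives is the cancelling drift in Step 1, which does not depend on the SD, and the lack of any statement of precision.

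A reader might also infer that the primary result is unsafe. It is not, on this ground. Allocation is 1:1, the primary contrast is duloxetine against placebo, and drift common to both arms cancels there.

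It can further be said that the sentence is an expectation rather than a decision rule, since no consequence of passing or failing is stated, and that interval reporting for a supporting check can be left to the SAP. That lowers the weight of the point. But the protocol does give both a purpose (exclude artefact) and a criterion (no significant change), and the criterion does not serve the purpose.

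Finally, there are other safeguards. Statistical Analysis has a quality-control pipeline, and Potential Problems or Pitfalls has scanning paused if drift is seen. The first screens individual scans for noise and movement. The second names signal-to-noise and contrast-to-noise for functional scans. Neither addresses a systematic shift in volume measured on the anatomical scans.

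**Conclusion.** The point holds in a limited form. A non-significant change, or one of about 0.75 cc, in 25 controls does not rule out scanner artefact. Tested against zero, a spurious gain of about 0.75 cc passes about 95% of the time at any SD, given the protocol's own ageing figure. Whether larger drifts would be missed is conditional: a net 1.5 cc change is very likely to be found if the SD is 2 cc and more likely than not to be missed if it is 5 cc. Those SDs, the two-sided 5% level and the 1.5 cc are assumptions.

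The consequence is confined to the pre-to-post claim in Anticipated Results and to comparisons of patients with controls. The randomised primary test is not affected by drift that the two arms share.

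**What to change.** In Sample Size Considerations, replace the criterion of no significant change with the following:
- Report the mean control change with its 95% CI, and compare it with the expected -0.75 cc rather than with zero.
- State how large a drift the interval excludes. Do not say artefact is ruled out if the interval includes drift as large as the observed within-arm gain.
- State that the primary conclusion rests on the randomised duloxetine-placebo contrast.

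I would not add a fixed equivalence margin. The documents give no effect in cc for partial relief from which to derive one. A margin as tight as 0.75 cc would also be narrower than the CI half-width even at an SD of 2 cc (0.83 cc).

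The cost is a few sentences, with no extra participants or scans. The downside is that the trial may well have to report that drift was not excluded.

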#### Potential Problems or Pitfalls:

The Radiology department performs routine quality control studies on the MR scanner, to insure that signal-to-noise ratio and contrast-to-noise ratio for functional scans are stable. If we detect drifts in these parameters, we would stop recruitment and pause scanning visits to attend to these problems. Such occurrences are rare, about once a year, and are usually handled by

Radiology in a routine fashion. There are a number of small technical details that are necessary to function properly for the fMRI studies. These are routinely tested prior to every fMRI scan, and inevitably occasionally fail. For this reason we have a complete second back-up system of the equipment that can replace any of the malfunctioning parts. Thus, we can almost always perform a scheduled scanning session for participants, and repair the damage subsequently. We expect that the scanner might fail in about 5% of the scans maximum, which may then need to be rescheduled, usually within 24 hours.

### **Anticipated Results:**

We expect to demonstrate that overall mean neocortical gray matter volume and regional gray matter density is increased from pre- to post-treatment in patients treated with duloxetine but not in placebo-treated patients.

For the secondary hypotheses, we will correlate gray matter volume and regional density measures with pain parameters, and we expect to demonstrate a correlation between the extent of pain relief and the change in magnitude of brain atrophy.
